## Abstract

**Background:**

Sleep is increasingly recognized as a fundamental determinant of health and brain function. Sleep difficulties are common in older adults, with a substantial proportion reporting problems initiating or maintaining sleep, which can negatively affect mental and physical health, cognitive function, and quality of life. Cognitive behavioral therapy for insomnia (CBT-I) is the gold-standard treatment for insomnia disorder; however, its reach is limited due to resource demands and a shortage of professionals that can deliver it. Digitally delivered CBT-I via eHealth platforms increases accessibility and has demonstrable effects but remains limited in many countries.

**Objective:**

The objective of this paper is to describe the protocol for the further development and evaluation of ASLEEP (Preventing and Treating Insomnia Symptoms in Midlife and Older Adults), a tiered, digitally delivered CBT-I intervention designed to reduce insomnia severity and improve related health outcomes in adults aged 50 years and older.

**Methods:**

The project will be conducted in 2 phases. Phase 1 focuses on refining and optimizing ASLEEP, developing an advanced CBT-I course, and integrating a nested trial into PROTECT (Platform for Research Online to investigate Cognition and Genetics in Ageing) Norge, a fully automated digital research platform. Phase 2 is a fully digital, 2-arm, waitlist-controlled randomized controlled trial, with 400 participants randomized 1:1 to the intervention or waitlist control and allocation stratified by age and insomnia severity. Outcomes will be assessed at baseline and at 3, 6, and 12 months, with a 15-month follow-up for the waitlist group. The primary outcome is insomnia severity measured by the Insomnia Severity Index. Secondary outcomes include sleep medication use, depression, anxiety, and cognition.

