### Power Analysis

At present, more than 3500 active participants with an active consent for contact in the PROTECT cohort. With the planned expansion, approximately 5000 participants are expected to be available at study initiation. Assuming that 15% of these (approximately 750 individuals) will meet eligibility criteria, we aim to recruit 500 participants (approximately 67% of those eligible). Allowing for 20% attrition in both arms prior to the 3-month follow-up, we expect 400 participants to be available for the primary efficacy analysis (200 per arm). This sample size provides more than 80% power to detect a small-to-medium effect size of 0.3 using a 2-sided significance level of α=.05. Applying ANCOVA in the primary analysis is expected to further increase statistical power, depending on the proportion of variance explained (*R*^2^) by baseline variables.

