### Limitations

Although the digital format of the ASLEEP study enables wide reach, adherence to treatment recommendations may be a challenge, as fully automated digital CBT-I programs have shown substantial variation in completion and adherence rates [40]. To address potential challenges with adherence, retention, and data completeness, a 20% dropout rate has been accounted for, and the PROTECT Norge help desk will provide proactive and continuous technical and procedural support, reminders, and guidance to encourage participant engagement throughout the trial.

Recruitment of 400 participants for randomization is ambitious given the current PROTECT Norge research willing cohort of approximately 3500 participants. While this represents a substantial recruitment pool, achieving the target sample size may be challenging; however, the ongoing expansion of the cohort toward 9000 registered participants, in line with PROTECT Norge’s established recruitment plan, is expected to strengthen recruitment feasibility.

Participation in PROTECT Norge requires a baseline level of digital competence, which supports delivery of this fully digital intervention but may limit generalizability to the broader population aged 50+ years, particularly those with less confidence in technology or internet use. However, a central element of the ongoing PROTECT Norge cohort expansion is a deliberate effort to broaden cohort diversity through targeted outreach to underrepresented demographic groups, recruitment strategies that extend beyond social media, and partnerships with community organizations and primary care providers. In addition, the PROTECT Norge help desk offers technical support intended to facilitate participation among individuals with lower digital competence. These efforts aim to mitigate selection bias in future phases of the research.

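### The number randomised is 400 in the abstract and limitations but 500 in the power section; at 400 with the planned 20% attrition, unadjusted power is about 76%, not above 80%

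*Protocol article*

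**What the plan says.** The sample size appears in three places in the protocol article.

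- Abstract, Methods: a two-arm trial "with 400 participants randomized 1:1 to the intervention or waitlist control".
- Power Analysis: "we aim to recruit 500 participants (approximately 67% of those eligible"). The next sentence begins "Allowing for 20% attrition in both arms prior to the 3-month follow-up" and continues "we expect 400 participants to be available for the primary efficacy analysis (200 per arm"). This sample is said to give "more than 80% power to detect a small-to-medium effect size of 0.3" at a two-sided 5% level. ANCOVA is mentioned as a further gain that depends on the variance explained; no value is given.
- Limitations: "Recruitment of 400 participants for randomization is ambitious given the current PROTECT Norge research willing cohort of approximately 3500 participants". The paragraph before it says that "a 20% dropout rate has been accounted for".

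The Randomization and Masking section adds that allocation is 1:1 and follows baseline assessment and confirmation of eligibility.

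**The concern.** In the power section 400 is what remains after attrition. In the abstract and the limitations it is the number entering randomisation. With 20% attrition these are different quantities, and the document does not reconcile them.

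The number randomised is the recruitment target. A team working from the abstract would stop at 400 and, on the protocol's own attrition assumption, analyse fewer participants than the power statement requires. The limitations paragraph also judges feasibility against 400; if 500 is needed, it understates the task by 100 people. The article is the stage 1 registered report, and trial registration and the ethics application are still to come, so an uncorrected figure could pass into both.

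**Working it through.** **Inputs, all from the protocol article**

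- Standardised difference d = 0.3, two-sided α = 0.05, power above 80% (Power Analysis)
- Attrition 20% in both arms before the 3-month follow-up (Power Analysis; a 20% dropout is also cited in Limitations)
- Allocation 1:1 (Randomization and Masking)
- Number randomised: 400 (Abstract; Limitations). Number recruited: 500 (Power Analysis)

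**Which number is the number randomised?** The power section places the loss within arms. Arms exist only after allocation, so the 500 before that loss are the randomised participants.

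**Formula.** For n analysed per arm, the normal approximation is power = Φ(d·√(n/2) − 1.96). The noncentral t result is given beside it.

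**Step 1: reproduce the protocol's figure.** 500 × 0.8 = 400, or 200 per arm. d·√(200/2) = 0.3 × 10 = 3.00, and Φ(3.00 − 1.96) = 85.1% (t test 84.9%). The claim of more than 80% is correct for 200 analysed per arm, without covariate adjustment.

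**Step 2: take 400 as randomised.** 400 × 0.8 = 320, or 160 per arm. d·√(160/2) = 0.3 × 8.944 = 2.683, and Φ(2.683 − 1.96) = 76.5% (t test 76.3%).

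**Step 3: effect detectable with 80% power at 160 per arm.** (1.96 + 0.8416) × √(2/160) = 0.313 (t test 0.314), against the 0.3 claimed.

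**Step 4: number needed for 80% power at d = 0.3.** n = 2 × (1.96 + 0.8416)² / 0.3² ≈ 174.4, so 175 per arm (t test 176). That is 350 to 352 analysed. Dividing by 0.8 gives 438 to 440 randomised. Put the other way, 400 randomised gives 352 analysed only if attrition is no more than 1 − 352/400 = 12%.

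**Step 5: what ANCOVA could recover.** The protocol gives no R², so a range is shown. The residual SD is √(1 − R²), with normal approximation.

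| R² | Power, 160 per arm | Power, 200 per arm |
|---|---|---|
| 0 | 76.5% | 85.1% |
| 0.05 | 78.6% | 86.8% |
| 0.10 | 80.7% | 88.5% |
| 0.20 | 85.1% | 91.8% |
| 0.30 | 89.4% | 94.8% |

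At 160 per arm, 80% is reached when R² = 1 − 160/174.4 ≈ 0.083. On the t-test basis, 1 − (0.3/0.314)² gives about 0.09.

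**The case against.** The strongest reply is that the power section, the only place where the sample size is derived, is correct. On that view 500 is the real target, the analysed number was carried by mistake into the abstract and limitations, and the 76% describes a trial nobody intends. The statement that dropout has been accounted for also fits 500. This is the likeliest explanation, and it means the 76% is conditional on 400 being the true target. It does not remove the contradiction: two sections give 400 explicitly as the number randomised, and nothing says which figure governs.

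A second reply is that 500 could be the number consenting, with 400 of them randomised. The power section rules this out by placing the attrition within arms and before the 3-month visit.

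A third is that the primary analysis is an ANCOVA adjusting for baseline ISI, demographics, PHQ-9 and GAD-7, so unadjusted power is pessimistic. This stands as a limit on the size of the problem, since a small R² is enough. But the power claim is made before adjustment, with ANCOVA named only as an additional, unquantified gain.

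The planned multiple imputation is no answer either. It keeps every randomised participant in the analysis but does not by itself restore the information lost with missing 3-month ISI scores, and the power section itself counts only those left after attrition.

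Finally, no stopping rule is tied to 400, so an early halt to recruitment is a risk and not a stated plan.

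**Conclusion.** Wrong as written. The protocol gives two incompatible numbers randomised, 400 and 500, and its power claim belongs only to 500. If 400 is the true target, unadjusted power for d = 0.3 is about 76%, some 8.6 percentage points below the 84.9% that the power section's own sample delivers and about 4 points below the 80% threshold. This rests on 20% attrition, equal arms, a two-sided 5% test and no credit for covariate adjustment, which is the basis on which the protocol makes its claim. The loss is modest and could be recovered with an R² of about 0.08 to 0.09. The inconsistency still has to be resolved, because the recruitment target is a basic design figure.

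**What to change.** State one randomisation target throughout.

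- **If 500 is intended**, which is what the only derivation supports: change the Abstract and the Limitations to 500 randomised (250 per arm), with 400 expected in the primary analysis, and judge recruitment feasibility against 500. In the Power Analysis, say that the 500 are randomised, not only recruited.
- **If 400 is intended**: rewrite the Power Analysis for 320 analysed (160 per arm). Give unadjusted power of about 76% at d = 0.3 and a detectable effect of about 0.314 at 80% power. If the 80% claim is to be kept through ANCOVA, state the R² it requires (about 0.09) and justify that value.

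Use the chosen figure in the trial registration and the ethics application as well. The cost is wording only, since recruitment has not begun. Under the second option the stated power becomes less favourable.

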**Results:**

The project started in January 2026, with funding awarded. As of February 2026, phase 1—intervention optimization and development—is underway. Ethics approval for ASLEEP has not been submitted. Following completion of phase 1, phase 2, which includes a digital randomized controlled trial, will commence; as of February 2026, no participants have been recruited, and data collection and data analysis have not yet started. Short-term data collection is planned to be completed by summer 2028, with results disseminated in winter 2028.

**Conclusions:**

This trial will evaluate the short- and long-term effectiveness of a tiered digital CBT-I intervention for midlife and older adults. By leveraging the PROTECT Norge platform and if effective, ASLEEP may represent a scalable model for low-threshold, accessible prevention and treatment of symptoms of insomnia.

## Introduction

### The Role of Sleep in Healthy Aging and Brain Health

Sufficient nighttime sleep is vital for maintaining optimal daytime functioning and supporting overall health and quality of life. For most adults, this generally involves obtaining 6 to 9 hours of sleep per night [1]. With increasing age, meeting individual sleep needs in terms of both duration and quality becomes harder [2], and up to 50% of older adults report difficulties initiating or maintaining sleep [3]. Failure to meet sleep needs and chronic sleep deprivation impair mood and emotional regulation; disrupt multiple physiological systems and cognitive functions; weaken immune responses; and increase the risk of several noncommunicable diseases, including cardiovascular disease, diabetes, and obesity, as well as mental health disorders [4]. Beyond these individual consequences, sleep deprivation also carries societal costs, contributing to increased health care expenditures, reduced productivity, and higher rates of workforce absenteeism, collectively amounting to 1% to 3% of gross domestic product in OECD countries [5].

Poor sleep is associated with poorer brain health in midlife, suggesting that sleep is a potential target for maintaining brain health into older age [6]. Experimental studies have shown that sleep deprivation impairs the efficiency of the glymphatic system, a key pathway for clearing neurotoxic waste products from the brain during sleep [7]. This impairment has been associated with β-amyloid deposition in older adults, which may in turn contribute to Alzheimer disease risk [8]. These mechanistic insights provide one of several pathways that may help explain the observed epidemiological association between sleep deprivation in midlife and an increased incidence of dementia later in life [9]. Beyond experimental and epidemiological evidence, sleep is increasingly recognized as a vital public health priority [4] and has been formally positioned as an equal pillar of health alongside physical activity and nutrition [10], underscoring its essential role in maintaining both brain function and overall health and well-being.

### When Poor Sleep Develops Into Insomnia: Insomnia Treatment Using Cognitive Behavioral Therapy

Difficulties falling asleep or staying asleep, or waking too early are the defining symptoms of insomnia. Moreover, a symptom burden with a frequency equal to or exceeding 3 days per week, persisting for over 3 months, resulting in daytime impairment, warrants a diagnosis of chronic insomnia [11]. While general sleep deprivation is associated with widespread physiological and cognitive consequences across multiple systems, insomnia is notably characterized by a strong and well-documented bidirectional relationship with mental health conditions, particularly anxiety and depression [12]. According to the Harvey cognitive model, insomnia is not just a consequence of insufficient sleep; rather, maladaptive thoughts, heightened arousal, and counterproductive behaviors interact to maintain the disorder through a feedback loop of worry, arousal, and behaviors that make sleep more difficult [13]. Building on this model, cognitive behavioral therapy for insomnia (CBT-I) is currently the gold-standard treatment for chronic insomnia and is a highly effective and safe treatment [11]. CBT-I combines behavioral strategies (eg, sleep restriction, stimulus control, and relaxation), cognitive techniques (eg, restructuring unhelpful thoughts, mindfulness, and paradoxical intention), and educational elements, including psychoeducation and sleep hygiene, and is usually delivered by trained professionals, such as psychologists or psychiatrists, over several structured sessions tailored to the patient’s needs [14]. It is a resource-demanding treatment, and combined with a lack of professionals with the competency to deliver CBT-I, it is usually reserved for those with a severe diagnosis of insomnia [15]. In Norway, [name] has published a CBT-I–based self-help book targeting adults with insomnia. In a randomized controlled trial (RCT) among self-referred participants, the tools and strategies presented in the book improved sleep, reduced use of sleep medication, and slightly decreased depressive symptoms compared with standard sleep hygiene advice [16]. A subsequent RCT among general practitioner–referred patients showed similar benefits, including reductions in sleep medication use and anxiety, as well as improved sleep outcomes [17]. These studies indicate that the self-help book is an effective low-threshold intervention for adults with insomnia in both community and primary care settings.

### eHealth Platforms for Increasing the Reach and Dissemination of CBT-I

The continuing digitization of people’s daily life has paved the way for new platforms delivering CBT-I via the internet (eCBT-I). eCBT-I offers wide reach and accessibility and serves as an effective alternative or supplement to traditional, in-person-delivered CBT-I [18]. However, access to evidence-based, eCBT-I programs, such as SLEEPIO [19] and Somryst [20], which are available by prescription in some health care systems, remains limited in many countries, including Norway.

The ASLEEP project (Preventing and Treating Insomnia Symptoms in Midlife and Older Adults) aims to enhance access to sleep education and insomnia symptom treatment by leveraging eHealth technologies. The intervention is based on the aforementioned CBT-I–based self-help book [16] and is tailored to the needs of an aging population through a tiered delivery model. The project is supported by the Platform for Research Online to Investigate Cognition and Genetics in Ageing Norge (PROTECT Norge) [21], which was initiated by the Centre for Age-Related Medicine (SESAM) at Stavanger University Hospital in 2020. PROTECT Norge is a digital, prospective research cohort with yearly follow-ups. Focusing on the brain aging, it assesses physical and mental health and lifestyle factors through validated questionnaires, as well as cognitive function using a neuropsychiatric test battery. In addition, the PROTECT infrastructure, originating from University of Exeter and Kings College London in the UK, includes a built-in research infrastructure designed to support large-scale digital RCTs [22,23]. The PROTECT Norge cohort [21] currently consists of 5547 registered individuals, who primarily have been recruited through social media, particularly Facebook. Interested individuals self-refer and are directed to the PROTECT Norge study website [24], where they complete eligibility screening, registration, and informed consent through a secure, fully automated online process. Once enrolled, participants complete annual validated cognitive and mental health assessments for up to 10 years and provide detailed information on lifestyle, medical, and demographic factors. Participants are also asked to provide consent for contact (C4C), which has been granted by 94% of PROTECT Norge participants [21]. Combining this with the PROTECT research infrastructure, which enables the conduction of nested studies, PROTECT Norge is well placed to deliver large-scale interventions and clinical trials in a time- and resource-efficient manner within the PROTECT Norge study trajectory.

To prevent the development of insomnia and promote good sleep, the ASLEEP intervention offers a basic course (tier 1). Supported by the PROTECT Norge infrastructure, a screening procedure will be developed to flag individuals with symptoms of insomnia of a degree that suggest the need for more intensive eCBT-I treatment and to guide those individuals to an advanced course (tier 2). The PROTECT Norge research infrastructure has already had its feasibility of delivering ASLEEP as a nested study in PROTECT Norge assessed, and the acceptability of the basic course content was also evaluated in the same study by this group ([name]; [name], PhD; [name]; et al; unpublished data; November 2025).

This paper describes the protocol for the ASLEEP project, including further development of the ASLEEP intervention to include an advanced course and its digital delivery (phase 1), as well as the evaluation of its effectiveness (phase 2) through a 2-arm RCT, with a waitlist design. The RCT will be conducted entirely digitally and facilitated by the PROTECT Norge research infrastructure.

The objectives of the ASLEEP project are to:

Further develop the ASLEEP intervention, an eCBT-I–based, tiered sleep program, including an advanced course aimed at reducing insomnia symptoms in adults aged 50 years and older.Conduct short- and long-term evaluations using the PROTECT Norge infrastructure to assess the effectiveness of the ASLEEP advanced course on sleep-related outcomes among midlife and older adults.Evaluate the effectiveness of ASLEEP on established outcomes that exist concomitantly or are related to insomnia symptoms, such as medication use, depression, anxiety, and cognitive function.

### Hypotheses

Our first hypothesis (H1) is that further development of the ASLEEP intervention—an eCBT-I–based, tiered sleep program—and its subsequent dissemination within the PROTECT Norge cohort will lead to a significant reduction in insomnia symptoms among individuals aged 50 years and older compared with waitlist control group.

Our second hypothesis (H2) is that ASLEEP will result in short-term improvements in sleep outcomes (Insomnia Severity Index [ISI] score and sleep medication use) among midlife and older adults, and these improvements will be sustained in the long-term.

Our third hypothesis (H3) is that ASLEEP will not only improve sleep outcomes but also lead to significant reductions in symptoms of depression, anxiety, and cognitive decline among midlife and older adults compared to a waitlist control group.

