### Eligibility Criteria

Inclusion criteria are as follows: participants must have completed the ASLEEP basic course, have an ISI score of 10 or higher, and have an insomnia duration exceeding 3 months.

Exclusion criteria are as follows: participants with insomnia symptoms that stem from other sleep disorders, including obstructive sleep apnea, restless legs syndrome, parasomnias, and hypersomnia, will be screened for based on selected items (Q2, Q6, Q7, and Q9) from the Global Sleep Assessment Questionnaire [32].

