### Outcomes

Study outcomes will be evaluated using validated instruments to capture the effects of the intervention on sleep, cognition, and related mental health domains through PROTECT Norge built-in clinical trials infrastructure. The primary outcome is insomnia severity, assessed using the ISI. All other outcomes are considered secondary outcomes (see Table 2 for details). Use of sleep medication is a secondary outcome and will be captured on a daily interval through the digital sleep diary.

**Table 2. T2:** Screening instruments and outcome measures used in the study, assessed through the Platform for Research Online to Investigate Cognition and Genetics in Ageing (PROTECT) Norge infrastructure.

Short name	Long name	Details	Time frame	Assessment points
ISI	Insomnia Severity Index [25]	7 items; scale 0-28, higher scores indicate more severe insomnia symptoms.	Past 2 wk	Screening/baseline + all follow-ups
SPD	Sleep problem duration item	One item assessing duration of sleep problem, scored 0=no sleep problem to 3=3 months or more	Current	Screening
GSAQ	Global Sleep Assessment Questionnaire [32]	Four separate items scored 0-4 will be used to screen for sleep disorders	Past 4 wk	Screening
FLAME	Factors of Longitudinal Attention, Memory and Executive Function [31]	Computerized neuropsychological battery with 8 tests. Gives composite score combining subscores on domains such as attention (speed and accuracy), memory, and executive function; higher scores reflect better overall cognitive performance.	Current	Baseline + all follow-ups
PHQ-9	Patient Health Questionnaire [33]	9 items; scale 0-27, higher scores indicate more severe depressive symptoms.	Past 2 wk	Baseline + all follow-ups
GAD-7	Generalized Anxiety Disorder scale [34]	7 items; scale 0-21, higher scores indicate more severe anxiety symptoms.	Past 2 wk	Baseline + all follow-ups

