Missing 3-month ISI and any missing baseline covariates will be handled using multiple imputation by chained equations (MICE). Imputation models will include all variables specified for the substantive model plus auxiliary variables given by 3-month measures of Patient Health Questionnaire-9, Generalized Anxiety Disorder-7, and FLAME. A total of *m*=100 imputed datasets will be generated, using logistic regression for dichotomous variables and otherwise predictive mean matching (*k*=5). Each imputed dataset will be analyzed with the primary ANCOVA, and effect estimates and standard errors will be combined using Rubin rules.

Supplementary analyses will assess the complier average causal effect. Sensitivity to missing not at random dropouts will be explored in a tipping-point (delta) analysis, by applying additive shifts to the imputed three months ISI scores separately by arm. In case of substantial skewness of the outcome, explorative sensitivity analyses will apply either Box-Cox transformation of the outcome or other regression models.

For the assessment of long-term effects on insomnia symptoms, there is no control group; thus, no conclusions will be drawn regarding treatment effects. The longitudinal development of ISI scores from baseline to 3, 6, and 12 months will be studied in linear mixed models, including random intercepts and slopes to allow for correlation between repeated measurements. Data from the original intervention arm will be combined with the (3 mo + delayed) data from the original waitlist arm for these analyses. Time since baseline (updated baseline for the waitlist arm) will be treated as a categorical variable.

Secondary outcomes will be analyzed similarly to ISI scores, with assessment of treatment impact at three months and longitudinal descriptive analysis of long-term trajectories, including covariance with insomnia symptoms. However, all secondary analyses will be exploratory.

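### The full PHQ-9 total includes a sleep item, so on its own it cannot show that mood improved as well as sleep, as H3 expects

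*Protocol article*

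**What the plan says.** The third hypothesis (Introduction, Hypotheses) states that "ASLEEP will not only improve sleep outcomes but also lead to significant reductions in symptoms of depression, anxiety, and cognitive decline", with the waitlist group as comparator. Table 2 under Outcomes gives the PHQ-9 as the depression measure: "9 items; scale 0-27, higher scores indicate more severe depressive symptoms". All nine items are scored, and no other depression measure is listed.

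The same section says: "The primary outcome is insomnia severity, assessed using the ISI". Under Eligibility Criteria, participants must "have an ISI score of 10 or higher, and have an insomnia duration exceeding 3 months".

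Statistical Analysis says of the other outcomes: "Secondary outcomes will be analyzed similarly to ISI scores, with assessment of treatment impact at three months". It adds a "longitudinal descriptive analysis of long-term trajectories, including covariance with insomnia symptoms" and states that "all secondary analyses will be exploratory".

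The article does not comment on the overlap between the PHQ-9 and insomnia symptoms.

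**The concern.** H3 presents lower depressive symptoms as a benefit on top of better sleep. One PHQ-9 item, scored 0 to 3, asks about disturbed sleep. The article does not list the items; this is standard content of the instrument it names. With entry restricted to people with insomnia, the item can be expected to be raised at baseline, and it covers the symptom the course is built to change.

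If the course works on its primary outcome, the PHQ-9 total should fall somewhat even if every other depressive symptom stays where it was. A 3-month difference in the total would then look like support for H3 while partly repeating the ISI result. The planned study of how depression and insomnia move together has the same difficulty, because the two scores share content. What is at stake is the interpretation of one named secondary outcome.

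**Working it through.** **The plan's own figure.** Power Analysis expects 200 analysed per arm and claims more than 80% power for a standardised effect of 0.3 at two-sided 0.05. By the normal approximation, power = Φ(d·√(n/2) − 1.96) = Φ(0.3 × 10 − 1.96) = Φ(1.04) = 0.851. Recruitment also agrees: 400 / (1 − 0.20) = 500. The statement reproduces. It concerns the ISI comparison and is not affected by this point.

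**Decomposition.** Write the PHQ-9 total as T = S + M, where S is the sleep item (0-3) and M the other eight items (0-24).
- Between-arm difference: Δ(T) = Δ(S) + Δ(M). If nothing but sleep changes, Δ(M) = 0 and Δ(T) = Δ(S).
- Covariance: Cov(T, ISI) = Cov(S, ISI) + Cov(M, ISI). The first term is expected to be positive because both scores record disturbed sleep.
- Ceiling: S carries at most 3 of 27 points, or 11% of the range.

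**Size when only the sleep item moves.** The article gives neither a PHQ-9 SD nor an item-level change, so both are assumed: Δ(S) of 0.3 to 0.8 points, and a total-score SD of 4 to 5, taken as the same at baseline and 3 months. Then d = Δ(S) / SD.

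| Δ(S) | SD 5 | SD 4 |
|---|---|---|
| 0.3 | 0.3/5 = 0.06 | 0.3/4 = 0.075 |
| 0.8 | 0.8/5 = 0.16 | 0.8/4 = 0.20 |

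**Chance of a nominally significant benefit with 200 per arm,** by the same formula and with no change in mood:
- d = 0.06: Φ(0.6 − 1.96) = Φ(−1.36) = 9%
- d = 0.20: Φ(2.0 − 1.96) = Φ(0.04) = 52%

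With no effect at all, the chance in that direction is 2.5% (half of the two-sided 5%). Covariate adjustment sharpens the test. With an assumed R² of 0.4 the SD is multiplied by √0.6 = 0.775, and the two chances become 12% and 73%.

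**After removing the item.** The direct contribution of S to the contrast and to the covariance is zero by construction.

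**The case against.** The strongest reply is that the article makes all secondary analyses exploratory, so no confirmatory depression claim rests on the PHQ-9. That stands, and it limits the weight of the point. It does not remove the overlap from the estimate, and H3 is still a stated hypothesis in a stage 1 registered report.

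A second reply is that H3 names a further outcome and does not claim an effect independent of sleep. This also stands. The third objective describes these outcomes as concomitant with or related to insomnia, and the Introduction describes a two-way relationship between insomnia and mental health. A reader might infer that H3 asserts a sleep-independent or mediation-type effect; the documents make no such claim. The narrower difficulty remains: the total cannot separate improved mood from improved sleep.

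A third reply is that item-level sensitivity analyses commonly sit in a full protocol or SAP, which is not shown. The point does not depend on that omission. The article itself fixes the 0-27 total as the depression measure and links it to insomnia symptoms.

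Three stronger readings are tempting and unsupported:
- That H3 cannot be judged at all. The item is one of nine, and the GAD-7 and FLAME parts of H3 are untouched.
- That the overlap is a large share of the effect the trial is sized for. The 0.3 in Power Analysis belongs to the primary comparison; nothing was sized on the PHQ-9.
- That the overlap explains the slight fall in depressive symptoms reported for the source self-help book. The article gives no instrument or figure for that result.

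**Conclusion.** The point holds in a limited form. With the full PHQ-9 total as the only depression measure, in a sample selected for insomnia, sleep improvement alone can lower the depression score and adds built-in covariance with the ISI. The total by itself therefore cannot show that mood improved as well as sleep.

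The contribution is about d = 0.06 to 0.20. That range rests entirely on the assumed item shift and SD, and its upper end pairs the largest shift with the smallest SD. The calculation shows what the overlap could contribute; it does not show that an observed PHQ-9 reduction would be due only to sleep. Using the PHQ-9 as a baseline covariate and as an imputation auxiliary is not a problem.

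**What to change.** Keep the nine-item total as the listed secondary outcome and as the baseline covariate. Prespecify two companion analyses on the PHQ-9 without its sleep item (eight items, 0-24): the same 3-month contrast, and the covariance with the ISI. Report both scores side by side, and state that H3's depression claim will be read as additional to sleep only if the eight-item result supports it. A sentence acknowledging the overlap belongs with the limitations.

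Replacing the validated total altogether is not needed. The eight-item score is less comparable with other trials, and reporting the total beside it offsets that. The cost is one more analysis. No new data collection should be needed, because all nine items are administered anyway; the team should confirm that item responses are stored and not only the total. As of February 2026 no participants had been recruited, so the change can be made before any data are seen.
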